# Impact of Dance or Music and Meditation on the Progression of Parkinson Disease With Mild or Moderate Severity: Protocol for a Pilot Randomized Controlled Trial

**DOI:** 10.2196/59018

**Published:** 2024-10-29

**Keywords:** music therapy, dance therapy, neurodegenerative disorders, meditation, quality of life, music, pilot study, Parkinson disease, well-being

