**Objective:**

This study aims to evaluate the effectiveness of dance or music and meditation on PD progression, cognitive functions, mood, behavior, and caregiver burden.

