**Conclusions:**

This study aims to provide significant insights into the effectiveness of dance or music and meditation in improving the quality of life and slowing the progression of PD. The findings are anticipated to support using these nonpharmaceutical therapies as complementary approaches to managing PD.

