### Aims

#### Primary End Point

The primary end point is to examine the effect of dance or music and meditation on the progression of mild and moderate PD using the Unified Parkinson’s Disease Rating Scale (UPDRS) I-III and Parkinson’s Disease Questionnaire-39 (PDQ-39) scores in patients with PD.

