All participants will be instructed to follow their daily routine and normal medication schedule. They will be instructed to keep the program coordinator informed if they make any significant changes to their treatment or their medication dosage or schedule. The participants in the intervention group will be asked to commit to the program and to take part in music or dance and meditation sessions thrice, weekly, for 6 months. On a weekly basis, patients should attend at least 1 session in physical presence, while the other sessions will be monitored through videoconferencing and home-based logs.

The patients will also be provided with the recordings of videos with instructions and a breakdown of each activity taught during the face-to-face sessions, making it easier for the participants to practice at home. A complete audio of the guided meditation schedule will be shared with the patients as well. The patients will be instructed to maintain an activity logbook documenting their adherence to home-based practice. Class attendance will be monitored and documented.

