### Data Analysis

IBM SPSS software will be used for the statistical analysis. Descriptive statistics will summarize the demographics, health conditions, and clinical outcomes at all 3 time points. Categorical variables including the Likert rating scales will be expressed in percentages and frequencies. The median and mode will also be ascertained for these data. Additionally, chi-square tests will be conducted, and *P* values will be ascertained to decipher the difference between the 2 groups against each outcome variable throughout the 3 time points.

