### Limitations and Future Implications

However, the study might be subject to some limitations. The 2 limitations to consider are the small sample size and the short duration of the study. A 6-month timeframe may not be sufficient to observe changes in nonmotor symptoms. Future larger, longitudinal RCTs are warranted to verify results. Motor and nonmotor symptoms of PD such as motor disability, gait and balance difficulties, speech disability, and pain are likely to hinder participation in activities such as dance and music. To compensate for this, each session will be customized according to the participants’ needs and abilities. Additionally, the results might be confounded by factors such as changes in medication or differences in baseline medication taken by the patient. Therefore, any changes made to lifestyle and medication over the course of the study will be constantly monitored. This paper will build upon previous research and delve into the effectiveness of non-pharmaceutical therapies in possibly delaying the progression of PD.

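### The trial is titled a pilot, but its objective, P-value analysis and expected conclusion are those of an effectiveness trial, which 15 v 13 completers cannot carry

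*Protocol article*

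**What the plan says.** **Pilot wording.** The title reads "Protocol for a Pilot Randomized Controlled Trial", and the keywords list the work as a pilot study. Limitations and Future Implications names the small sample as a limitation and adds "Future larger, longitudinal RCTs are warranted to verify results".

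**Effectiveness wording.**
- Abstract, Objective: "This study aims to evaluate the effectiveness of dance or music and meditation on PD progression, cognitive functions, mood, behavior, and caregiver burden".
- The first of the Aims in Methods is worded thus: "The primary end point is to examine the effect of dance or music and meditation on the progression of mild and moderate PD", measured by UPDRS I-III and PDQ-39. Neither the primary nor the secondary end points concern feasibility.
- Data Analysis: "chi-square tests will be conducted", with P values for the two groups on every outcome variable. The section names no between-group difference and no confidence interval.
- Expected Outcomes: significant improvement is anticipated in both motor and nonmotor aspects.
- Abstract, Conclusions: "The findings are anticipated to support using these nonpharmaceutical therapies as complementary approaches to managing PD". The closing Conclusions section says much the same.

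**Size.** Study Design plans 15 participants per arm. Results reports 30 recruited and 28 completing, 15 in the intervention group and 13 in the control group. No alpha, power, effect size or SD is given.

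**Process data.** The Intervention Group section says "Class attendance will be monitored and documented" and asks patients to keep a logbook of home practice.

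**The concern.** The document sets up two incompatible readings of the same result. Under the pilot reading, the scale differences are rough estimates that feed a later trial. Under the effectiveness reading, a P value on UPDRS I-III or PDQ-39 decides whether the therapy works, and the conclusions already say which way the decision is expected to fall.

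What is at stake is how the result will be used. In a trial this small, a difference has to be large to reach significance. If the true effect is small or moderate, those that do reach it will be too large on average. A non-significant result would leave moderate effects open but could be read as evidence against the therapy. A P value without a difference and an interval shows the reader neither problem.

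**Working it through.** **Inputs.** Planned 15 per arm (Study Design); completers 15 and 13 (Results). Alpha, sidedness, effect size and SD are not stated, so the planned 30 cannot be reproduced. The completer shares can be: 15/28 = 53.6% and 13/28 = 46.4%, which match the printed 54% and 46%.

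**Assumptions.** Two-sample comparison of means, two-sided alpha 0.05, true effects of 0.3 to 1.0 SD. The t-test is a benchmark for what data of this size can show; it is not the analysis the article names.

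**1. Precision.** SE = sqrt(1/15 + 1/13) = 0.379 SD. With 26 degrees of freedom, t(0.975) = 2.056. Half-width = 2.056 × 0.379 = 0.78 SD. This is also the smallest observed difference that reaches P<0.05. With all 30 followed, SE = sqrt(2/15) = 0.365 and the half-width is 2.048 × 0.365 = 0.75 SD, so the two losses matter little.

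**2. Power** (noncentral t, noncentrality = true effect / SE) **and overstatement** (mean absolute estimate among significant results, divided by the true effect; 200,000 simulated trials per row), both for 15 v 13:

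| True effect (SD) | Power | Overstatement if significant |
|---|---|---|
| 0.3 | 12% | 3.0-fold |
| 0.5 | 25% | 1.9-fold |
| 0.8 | 53% | 1.3-fold |
| 1.0 | 72% | 1.2-fold |

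Power of 80% is reached only at a true effect of 1.10 SD (1.06 SD with 15 v 15).

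**3. Sensitivity to baseline adjustment.** With an assumed baseline-to-follow-up correlation of 0.7, residual SD falls by sqrt(1 − 0.49) = 0.714. The half-width becomes about 0.78 × 0.714 = 0.56 SD, the effect detectable with 80% power 1.10 × 0.714 = 0.79 SD, and power at 0.5 SD about 43%. This is better, but still not a basis for judging effectiveness at moderate effects.

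**4. What a null result could say.** An estimate of zero would have an interval of about −0.78 to +0.78 SD. That excludes effects larger than about 0.8 SD but not moderate ones.

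**5. Retention.** 28/30 = 93%, exact 95% CI 78% to 99%. By arm: 15/15 (78% to 100%) and 13/15 (60% to 98%).

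**The case against.** The case on the other side has real substance.

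- **The label may be loose.** The article never defines pilot as feasibility-only; it could mean a small preliminary efficacy trial. This stands as far as it goes, but a preliminary trial still does not support a conclusion, written before the results, that the findings will favour use.
- **The article already hedges.** It names the small sample and calls for larger trials. This is partial mitigation. It leaves the effectiveness objective and both conclusions unchanged.
- **The figures describe a test that is not planned.** True: only chi-square tests are named. The calculation shows what 28 patients can tell about a mean difference under any reasonable analysis of these scales, and is labelled as assumed.
- **Effects might be large.** The only before-and-after figures with SDs in the article, from a cited virtual reality dance study, give 2.1 / 2.31 = 0.9 SD on the Berg Balance Test and 2.2 / 1.55 = 1.4 SD on the Beck inventory (each divided by the root mean square of the two SDs). These are within-group changes on scales that are secondary here, so they do not establish a large between-group effect. They do show that 0.3 to 0.5 SD is a choice, and the overstatement is modest at 0.8 SD and above.

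Three stronger readings are tempting and are not supported:
- **That the pilot data go unused.** Retention by arm is already reported. Attendance and logbook adherence have no stated use here, but their tabulation, like that of the SDs, may be left to a full protocol or analysis plan that is not shown.
- **That a null result would be uninformative.** It could exclude very large effects.
- **That the sample size is itself an error.** No power is claimed, so there is no stated figure for it to fail.

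**Conclusion.** The point holds as a mismatch, in the current text, between the pilot label and the objective, primary end point, P-value analysis, anticipated significant improvements and expected support for use. It does not depend on any document that is not shown.

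Its size rests on assumed values: a two-sample comparison at two-sided 0.05, and true effects that the article does not give. The risk of a misleading significant result is large at 0.3 to 0.5 SD and small at 0.8 to 1.0 SD. The risk of missing a real effect runs from 88% at 0.3 SD to 28% at 1.0 SD (100% minus the power above).

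The trial remains sound as a source of preliminary estimates. What needs correcting, before the results are read as evidence for or against the therapy, is the stated inference and the conclusion fixed in advance.

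**What to change.** 1. **Data Analysis:** make the primary analysis of UPDRS I-III and of PDQ-39 a between-group difference with a 95% CI, reported as a preliminary estimate, in place of chi-square P values.
2. **Data Analysis:** state that neither a significant nor a non-significant P value will be read as showing or refuting effectiveness.
3. **Wording:** reword the abstract Objective, the abstract Conclusions, Expected Outcomes and the closing Conclusions to match. The expectation of support for use appears in two places, and both need changing.
4. **Optional:** summarise attendance and logbook adherence with CIs, and add the interval to the retention already reported (28/30, 78% to 99%). Data collection ended in February 2024, so any pilot aim or progression criterion added now must be labelled post hoc.

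The cost is wording and a short table from data already collected; no further enrolment is proposed. The downside is that the trial gives up a confirmatory claim.

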## Abstract

**Background:**

Parkinson disease (PD) is a progressive neurodegenerative disorder characterized by motor dysfunctions and nonmotor symptoms. Current treatments do not alter disease progression, highlighting the need for alternative therapies. Music, dance, and mindfulness meditation have shown the potential to improve symptoms and quality of life in patients with PD.

**Objective:**

This study aims to evaluate the effectiveness of dance or music and meditation on PD progression, cognitive functions, mood, behavior, and caregiver burden.

**Methods:**

This study is a single-blinded, longitudinal, parallel, randomized controlled trial. The participants consist of 30 patients with mild to moderate PD residing in Mumbai, India, who can physically participate in the activities. The exclusion criteria include advanced PD, severe balance issues, age >80 years, and other movement disorders. Participants in the intervention group will engage in dance or music sessions and guided meditation thrice weekly for 6 months. The control group will continue their usual activities and medication. The primary outcome is the progression of PD symptoms, measured using the Unified Parkinson’s Disease Rating Scale I-III, and quality of life, measured using the Parkinson’s Disease Questionnaire-39. The secondary outcomes include cognitive functions (Mini-Mental State Examination), mood (Beck Depression Inventory and Parkinson Anxiety Scale), mobility (timed up and go and Berg Balance Test), behavioral disorders (Questionnaire for Impulsive-Compulsive Disorders in Parkinson’s Disease Rating Scale), and caregiver burden (Zarit Burden Interview and Parkinson’s Disease Questionnaire-Carer).

**Results:**

Data collection was completed in February 2024, with 28 participants finishing the study (intervention group: n=15, 54% and control group: n=13, 46%). Data analysis is underway, with results expected to be published in December 2024.

**Conclusions:**

This study aims to provide significant insights into the effectiveness of dance or music and meditation in improving the quality of life and slowing the progression of PD. The findings are anticipated to support using these nonpharmaceutical therapies as complementary approaches to managing PD.

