### Assessments

All assessments will be conducted during the “on phase,” that is, during the phase when the PD medication is in effect. The outcomes will be assessed by a specialist nurse, a neuro-consultant, and a consultant psychologist. The neuro-consultant is a functional neurosurgeon with pioneering work in this field and more than 30 years of experience in movement disorder surgeries. The specialist nurse has been involved in the treatment of movement disorder patients for more than 26 years and is a certified UPDRS assessor. For the reassessments, the marker who conducted the initial assessment will conduct subsequent assessments.

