The study by Katlen da Silva et al [12] aimed to evaluate the effects of music-based physical therapy on individuals with PD in terms of muscle strength (Medical Research Council Test and Sitting-Rising Test), cognition (Trail Making Test), muscle strength, balance (BBT), and functional mobility (TUG). It was a controlled, nonrandomized clinical trial with an A-B-A design involving 13 individuals with PD. The results showed that music-based physical therapy helped improve balance and functional mobility in individuals with PD. However, these improvements were not maintained after the therapy was discontinued.

The study by Lihala et al [47] in India examined the impact of dance therapy on cognition, QoL, and motor symptoms in 10 patients with mild-to-moderate PD. The results showed improved cognitive function and QoL, as indicated by increased Montreal Cognitive Assessment scores and decreased PDQ-39 scores [47].

Lee et al [48] examined the effects of virtual reality dance exercises on patients with PD. They found that after 6 weeks of treatment, the experimental group showed significant improvements in BBT (from mean 46.0, SD 1.3 to mean 48.1, SD 3.0); activities of daily living (from mean 87.9, SD 1.4 to mean 91.1, SD 3.0); and Beck Depression Inventory (from mean 20.4, SD 0.9 to mean 18.2, SD 2.0) compared to the control group, highlighting a positive impact on these aspects for patients with PD [48].

The studies mentioned above highlight that dance, music, and mindfulness have improved motor and nonmotor symptoms, activities of daily living, balance, cognitive function, and QoL in patients with PD.

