### Conclusions

This study aims to provide significant insights into the effectiveness of dance or music and education in improving the QoL and slowing the progression of PD. The findings are expected to support the use of nonpharmaceutical therapies as a complementary approach to managing PD, offering potential benefits to both patients and their caregivers.

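### The trial is framed as testing slower Parkinson disease progression, but its design can estimate only a difference in on-medication symptoms and quality of life

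*Protocol article*

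**What the plan says.** All places are in the protocol article.

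**The claim.** The abstract's Background gives the rationale: "Current treatments do not alter disease progression, highlighting the need for alternative therapies". The Introduction makes the same contrast with medical and surgical treatment. The Objective is to "evaluate the effectiveness of dance or music and meditation on PD progression". The Primary End Point is an effect on the progression of mild and moderate disease, using UPDRS I-III and PDQ-39 scores. The abstract's Conclusions refer to "improving the quality of life and slowing the progression of PD" and the main Conclusions to "improving the QoL and slowing the progression of PD". The title and the Limitations section also use the language of progression. The main Conclusions add: "The findings are expected to support the use of nonpharmaceutical therapies as a complementary approach to managing PD".

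**The design.** Under Assessments, all measurements are made "during the phase when the PD medication is in effect". Reassessments provides for one follow-up within 6 months of allocation, the 3-month visit having been dropped. Under Intervention Group, sessions run for 6 months. Under Control Group, controls may join sessions once the study is over, with no assessment attached. Data Analysis still counts three time points.

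**The concern.** Set against treatments that are said not to alter progression, the promise of slowing it reads as a promise to change the disease course and not only to relieve symptoms. The only follow-up measurement, however, is taken while participants are on medication and during or at the end of the programme. A benefit that lasts only as long as the sessions would look the same as a slower disease.

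The article supplies an example of why this matters. Of a music-based physical therapy study it reports that "these improvements were not maintained after the therapy was discontinued". If the arms differ at follow-up, the current framing invites the reader to take the difference as slowed progression, and the data could not support that.

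**Working it through.** The plan states no effect size, SD, alpha or power, so there is no figure to reproduce. The question is whether the quantity claimed can be identified.

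**Inputs from the article**
- Medication state: on phase at every assessment (Assessments).
- Post-baseline assessments: one, within 6 months of allocation (Reassessments).
- Treatment: 6 months (Intervention Group), so the reassessment falls during or at the end of it.
- Controls: offered sessions after the study, not assessed on them (Control Group).
- Completers: 15 intervention, 13 control (Results).

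**Model.** Write the expected between-group difference at time t (years) as D(t) = s + b·t. Here s is a symptomatic offset present while sessions continue, and b is the difference in the yearly rate of progression.

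**One on-treatment visit at t = 0.5.** D = s + 0.5b is one equation in two unknowns. With illustrative values in UPDRS points, which are assumptions and not from the article:
- purely symptomatic: s = -4, b = 0 gives D = -4 + 0 = -4
- mixed: s = -2, b = -4 per year gives D = -2 - 2 = -4
- purely slowing: s = 0, b = -8 per year gives D = 0 - 4 = -4

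The three cannot be told apart. More participants would estimate D more precisely but would not split it. A visit earlier than 6 months changes the multiplier of b, not the number of equations.

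**What would separate the two**
- A visit after sessions stop, once any symptomatic effect has gone, would give a difference depending on b alone. None is described.
- A restored 3-month visit, as the three time points in Data Analysis might suggest, gives D(0.25) = s + 0.25b. Then b = [D(0.5) - D(0.25)] / 0.25, but only if the symptomatic effect is complete by month 3 and constant afterwards. If it is still growing, there are three unknowns and two equations.

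**Precision, a separate matter.** In SD units, the standard error of the difference is √(1/15 + 1/13) = √(0.0667 + 0.0769) = 0.379. With the t quantile on 26 degrees of freedom, 2.056, the unadjusted 95% CI half-width is 2.056 × 0.379 = 0.78 SD.

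**The case against.** The strongest defence is that the article often means something narrower. The abstract's Methods and the heading in Outcomes Measures define the primary outcome as progression of symptoms, scored by UPDRS I-III, and the Primary End Point ties progression to the UPDRS and PDQ-39 scores. On that definition the between-group difference is estimable. This stands: a reader might infer that the primary comparison itself cannot be estimated, and the documents do not support that. The narrower wording does not displace the broader claim, though, because the rationale, Objective and both Conclusions go beyond it.

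Other parts also stand:
- The Conclusions sentence is an aim, not a result. A reader might infer that slowing has been claimed as shown, but it has not. The sentence expecting support concerns only a complementary role in managing the disease.
- The article calls itself a pilot. Its Limitations section names small size, short duration and medication confounding, and asks for larger trials. Participants are told to keep their usual medication schedule and report changes.
- The cited music study was nonrandomised, had 13 participants, and lost its gains in balance and functional mobility. It shows that a reversible effect is plausible, not that this programme's effect is reversible.
- Low precision does not cause the identification problem and should not be offered as its measure.

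That the article condenses a fuller protocol does not answer the point. It fixes both the medication state and the reassessment schedule, and the fault lies in what is claimed from them.

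**Conclusion.** The point holds in a limited form. The trial can estimate a between-group difference in on-medication symptom severity and quality of life at the reassessment. It cannot attribute any part of that difference to a slower disease course, and the listed limitations do not say so. The framing should be corrected before results are reported.

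No number of UPDRS points expresses the defect, because the split between symptomatic benefit and slowing is undetermined at any sample size. The conclusion rests on two readings: that progression in the rationale and Conclusions means disease course, and that the single reassessment is the operative schedule. If a 3-month visit did take place, separation would still need the strong constancy assumption shown above.

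The half-width of 0.78 SD is only a secondary reason not to read a null result as absence of effect.

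**What to change.** - State the aim, and both primary outcomes, as the between-group difference with 95% CI in on-medication UPDRS I-III and in PDQ-39 at the reassessment. PDQ-39 keeps its place alongside UPDRS.
- Remove the wording on slowing, or an effect on, progression from the Objective, Primary End Point and both Conclusions. The title carries the same wording, so the results report should not inherit it.
- Add to Limitations that a temporary symptomatic benefit cannot be distinguished from a slower disease course.
- Replace the anticipated supportive findings in both Conclusions with a statement that the pilot estimates will inform a larger trial.
- Reconcile Reassessments (one follow-up, within 6 months) with Data Analysis (three time points), and say when the reassessment took place.
- Disclose that the rewording was made after data collection, which ended in February 2024.

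No new data are needed. The cost is a more modest stated claim and an openly dated change to the wording of the objective and primary end point of a registered trial.
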